### Outcome

2.19

#### Primary efficacy endpoints

2.19.1

We selected the PASI and BMI as primary endpoints, as they are well-established metrics for psoriasis lesions and obesity, respectively. Through expert panel discussion, a consensus-based decision was made to define the primary outcomes as the absolute change in PASI improvement score and the absolute change BMI at Week 8. The formulas for calculation are presented below:

(1) PASI improvement rate at week 8 = (baseline PASI score - PASI score at Week 8) / baseline PASI score × 100%.(2) Change in BMI at week 8 = baseline BMI - BMI at Week 8.

#### Secondary outcomes

2.19.2

After discussion, the experts reached the following conclusion:

1 Disease severity (assessed at weeks 4 and 8, unless specified)

(1) Improvement rates: PASI (Week 4 only), BSA, and TCM Syndrome score.(2) Calculated as: (baseline score - score at time point) / baseline score.

2 Metabolic and inflammatory parameters (change from baseline; Δ = baseline - week 4/8 value)

These types of parameters include: erythrocyte sedimentation rate (ΔESR), C-reactive protein (ΔCRP), body weight (ΔWeight), waist circumference (ΔWC), waist-to-hip ratio (ΔWHR), body mass index (∆BMI at Week 4 only),lipids and glucose metabolism.

3 Subgroup analyses (change from baseline in participants with abnormal values at baseline)

Additionally, a subgroup analysis was prespecified for patients with abnormal baseline metabolic parameters or metabolic syndrome. For these patients, changes from baseline in HbA1c, fasting serum insulin, uric acid, blood pressure, and lipid levels will be assessed at Weeks 4 and 8. This analysis is in line with methodologies described in previous literature. The changes will be calculated as follows:

Difference of blood pressure (Δsystolic BP) (55): In participants with baseline > 120/90 mmHg (Weeks 4, 8).Difference of fasting plasma glucose (ΔFPG): In participants with baseline > 6.1 mmol/L (Weeks 4, 8).Difference of glycated hemoglobin (ΔHbA1c): In participants with baseline > 6.0% (Weeks 4, 8).Difference of uric acid (∆UA): In participants with baseline > 416 μmol/L (men) or > 358 μmol/L (women) (Weeks 4, 8).

We will collect electronic data through Excel spreadsheets and use double data entry to validate key efficacy variables in real time, with data administrators reviewing data quality reports weekly. Only attending physicians, researchers participating in the clinical study, and monitors will have access to participants’ personal records, and they will handle them confidentially. Data will be processed anonymously, omitting any personally identifiable information of participants, and personal privacy, such as facial images, will be anonymized. Participants’ personal information will be stored in the hospital’s laboratory system and medical records. Researchers should preserve all research materials, including confirmations from all research participants (which can effectively verify different records, such as original hospital records), all original informed consent forms signed by research participants, detailed records of all clinical forms, and so on. Researchers should retain clinical trial data for 5 years after the termination of the clinical research work.

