All statistical analyses will be performed using a pre-specified statistical analysis plan. The primary analysis will use a linear mixed-effects model for repeated measures to analyze the changes from baseline in the continuous PASI score and BMI at week 8. As these will be pre-specified co-primary endpoints evaluating distinct therapeutic dimensions, no adjustment for multiple will be applied. Each endpoint will be tested independently at a two-sided significance level of *α* = 0.05. A similar approach will be used for continuous secondary outcomes (e.g., DLQI, WC, lipid profiles, inflammatory markers) will be presented as mean ± standard deviation for continuous variables and as frequencies (n) and percentages (%) for categorical variables. Within-group comparisons (e.g., baseline vs. Week 8) will be analyzed using paired t-tests for normally distributed data or Wilcoxon signed-rank tests for non-normally distributed data. Between-group comparisons will be performed using independent samples t-tests or Mann–Whitney U tests. Categorical outcomes will be compared using Chi-square tests (or Fisher’s exact tests). A two-sided *p*-value < 0.05 will be considered statistically significant. All analyses will follow the intention-to-treat principle. For exploratory outcomes assessed at extended time points (Weeks 12, 16, 24, and 32), the analysis will be primarily descriptive. Data are presented as mean ± standard deviation (or median with interquartile range for non-normally distributed data). No formal between-group hypothesis testing will be performed for these time points, as the data will be intended to illustrate long-term trends rather than confirm treatment efficacy. All statistical tests will be two-sided with a significance level of *α* = 0.05.

Pre-specified subgroup analyses will be performed to explore the heterogeneity of treatment effects on the primary outcomes. Interactions between treatment group and the following baseline covariates will be tested using the linear mixed model by including an interaction term: sex (male, female), age (< 45 years, ≥ 45 years), baseline BMI (< 28 kg/m^2^, ≥ 28 kg/m^2^), baseline disease duration (< 5 years, ≥ 5 years)

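### Within-arm paired tests in the subgroups with abnormal baseline values raise the chance of a false significant improvement through regression to the mean

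*Protocol article*

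**What the plan says.** Section 2.19.2 (Secondary outcomes), item 3, is headed "Subgroup analyses (change from baseline in participants with abnormal values at baseline". It gives cut-offs for four markers:

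- systolic blood pressure: "In participants with baseline > 120/90 mmHg (Weeks 4, 8"
- fasting plasma glucose: "In participants with baseline > 6.1 mmol/L (Weeks 4, 8"
- HbA1c: "In participants with baseline > 6.0% (Weeks 4, 8"
- uric acid: "In participants with baseline > 416" μmol/L for men, with a threshold of 358 for women

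Item 2 of the same section, "Metabolic and inflammatory parameters (change from baseline", defines change as baseline minus the week 4 or week 8 value, so a positive change is a fall. Table 1 shows one pre-treatment time point, week 0, and no separate qualifying measurement is mentioned.

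Section 2.21 (Statistical methods) then states: "Within-group comparisons (e.g., baseline vs. Week 8) will be analyzed using paired t-tests for normally distributed data or Wilcoxon signed-rank tests". It continues: "Between-group comparisons will be performed using independent samples t-tests or Mann–Whitney U tests". A two-sided p below 0.05 counts as significant. The section also says that subgroup results will be interpreted as exploratory and that no multiplicity adjustment is made for them. Regression to the mean is not mentioned there or in the Limitation section.

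**The concern.** For these four markers one reading does two jobs: it admits the patient to the subgroup and it is the starting point of the change. Part of any high reading is measurement error and short-term variation. A group chosen for high readings will therefore tend to read lower next time, whether or not anything was done to it. A paired test asks whether mean change is zero. In a group selected in this way, mean change is not zero under no effect, so the test can reject because of the selection alone.

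The practical risk is a significant within-arm fall in glucose, uric acid or blood pressure that looks like a metabolic benefit. With few patients per arm, one arm can cross the threshold by chance while the other does not. A significant verum arm beside a non-significant sham arm is easily misread as an effect of ACE.

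This differs from a general objection to within-group tests. Without selection on baseline, the paired test keeps its 5% level when there is no change.

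**Working it through.** **Inputs from the documents.** Cut-offs and change definition: section 2.19.2. Tests and two-sided alpha of 0.05: section 2.21. Arm size: section 2.11, which reproduces as (1.96 + 0.84)² × [0.60 × 0.40 + 0.25 × 0.75] / 0.35² = 7.84 × 0.4275 / 0.1225 = 27.36, rounded up to 28, and 28 / 0.80 = 35 per arm.

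**Inputs assumed.** The documents give neither the correlation r between a marker's baseline and follow-up values nor the share of participants above the cut-off. I took r from 0.5 to 0.95, cut-offs at c = −0.33, 0, 0.5 and 1.0 SD (about 63%, 50%, 31% and 16% abnormal), and 28 or 35 per arm.

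**Model.** Baseline X is standard normal. Follow-up is Y = rX + √(1 − r²)·e, where e is independent standard normal. There is no treatment effect and no true mean change. Only patients with X > c are kept, and the outcome is X − Y.

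**Expected spurious fall.** E(X − Y | X > c) = (1 − r) × φ(c) / [1 − Φ(c)]. At c = 0.5 and r = 0.7 this is 0.3 × 0.352 / 0.309 = 0.34 baseline SD. It is zero only if r = 1.

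**Per-arm rejection by the paired t-test, simulated, 35 per arm (nominal 5%):**

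| Share abnormal | Mean n per arm | r = 0.5 | r = 0.7 | r = 0.8 | r = 0.9 |
|---|---|---|---|---|---|
| 31% | about 11 | 45% | 29% | 19% | 11% |
| 50% | about 17 | 40% | 24% | 17% | 12% |
| 63% | about 22 (0.63 × 35) | 30% | 19% | 13% | 9% |

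Further results:

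- At r = 0.95 the rate is about 6–9%.
- With 28 per arm, 31% abnormal and r = 0.7, it is 22%.
- Whenever r ≤ 0.8, it is at least about 11–12% over the whole grid. The lowest values occur with 28 per arm.
- With 35 per arm, 31% abnormal and r = 0.7, at least one arm is falsely significant in about 49% of trials, per marker and visit. Two unbiased tests would give 1 − 0.95² = 9.8%. Verum alone is significant in about 21%.

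**Two controls.** Without selection on baseline, the paired test rejects in 4.7–5.2% of trials. In the selected subgroup, the between-arm test rejects in about 4–6% in every setting. The inflation therefore comes from combining baseline selection with a within-arm test. It is absent from the randomised comparison because both arms regress equally.

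**The case against.** **The link between the two sections is inferred.** Section 2.19.2 names no test for these subgroups, and the paired-test sentence in 2.21 is generic. The sentence before it, which is garbled, appears to extend the mixed model to continuous secondary outcomes. This stands as a limit on how firmly the plan can be read. Still, the paired-test sentence carries no exemption, so on its wording it covers these outcomes.

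**The trial's inference is between arms.** The design is sham-controlled, the hypothesis is superiority over sham, and between-group tests are planned. A reader might infer that the plan will produce false claims of metabolic efficacy. The documents do not support that: nowhere do they say that a within-arm p-value will count as evidence of efficacy, and the planned between-arm comparison keeps its level.

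**These are exploratory subgroups.** The metabolic co-primary endpoint is BMI in all participants, and lipids and glucose metabolism are also listed for the full sample. A reader might infer that the metabolic half of the dual-action claim rests on the affected outcomes. It does not. The exploratory label lowers the weight of the results, but it does not make zero change the right null for the within-arm test.

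**The size is assumed.** The 45% figure needs r = 0.5, and a stable marker is barely affected. Nothing in the documents says where each of the four markers lies. This stands: a false positive becomes more likely, not certain.

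**All participants receive diet and lifestyle education (section 2.12).** Within-arm change is therefore not a clean test of ACE in any analysis set. That is true, but regression to the mean adds a bias specific to the subgroups selected on baseline.

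**Conclusion.** The point holds in a limited form. For systolic blood pressure, fasting glucose, HbA1c and uric acid, the plan selects patients on the baseline from which it measures change, and it states within-group paired tests without exempting these outcomes. Those tests would have an inflated false-positive rate in either arm. The rate is roughly 11–45% at r = 0.9 down to 0.5 with 31% abnormal and 35 per arm, and about 6–9% at r = 0.95. These figures rest on a bivariate normal model and on assumed values of r and the share abnormal.

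The point is shown only for the four markers with stated cut-offs. Section 2.19.2 also names fasting insulin, lipids and a metabolic-syndrome group but gives no thresholds for them. The blood-pressure cut-off is a systolic/diastolic pair, so for that marker the argument works through its systolic part.

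The between-arm comparison, the co-primary endpoints and the sample size are unaffected. This is a minor correction to exploratory analyses.

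**What to change.** In sections 2.19.2 and 2.21:

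1. State that within-group paired tests do not apply to outcomes restricted to participants with abnormal baseline values.
2. Report these outcomes as the verum-minus-sham difference at weeks 4 and 8 with a 95% CI, preferably adjusted for the marker's baseline. The adjustment is for precision. The unadjusted between-arm comparison is already free of this bias.
3. Show within-arm changes descriptively, without p-values, and note that regression to the mean is expected in both arms.

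The cost is a few sentences and no new data. The within-arm p-values are lost, and the between-arm intervals will be wide, with perhaps 5 to 20 patients per arm in each subgroup.

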### Quality control

2.20

To ensure standardization and consistency in study implementation and data collection, all research personnel will undergo systematic and standardized training. The training curriculum will cover the following key areas: participant identification and screening procedures, standardized ACE operation protocols, methods for evaluating efficacy and safety outcomes, identification and management procedures for AEs, and standardized completion of case report forms. Furthermore, an independent quality monitoring committee consisting of three experts will be established to oversee trial conduct and data security throughout the study. This committee will be responsible for identifying and reporting any protocol deviations or adverse events in a timely manner and may recommend pausing the trial if necessary, thereby safeguarding trial quality and protecting participant rights to the greatest extent possible.

### Statistical methods

2.21

All participants who provided written informed consent and completed baseline assessments will be included in the primary analysis, consistent with the ITT principle. Data will be analyzed according to the group to which participants will be initially randomized, regardless of treatment adherence, protocol deviations, or loss to follow-up, to minimize selection bias and reflect real-world clinical effectiveness. For missing data, a stratified strategy will be adopted: preference will be given to filling in missing values using existing data through multiple imputation or mixed-effects models, while also conducting per-protocol set analyses (including only participants with ≥ 80% compliance) as sensitivity verification; for categorical data, if the proportion of missing values is ≤ 5%, the indicator will be directly excluded, and if it is > 5%, the FIML method will be used.

All statistical analyses will be performed using a pre-specified statistical analysis plan. The primary analysis will use a linear mixed-effects model for repeated measures to analyze the changes from baseline in the continuous PASI score and BMI at week 8. As these will be pre-specified co-primary endpoints evaluating distinct therapeutic dimensions, no adjustment for multiple will be applied. Each endpoint will be tested independently at a two-sided significance level of *α* = 0.05. A similar approach will be used for continuous secondary outcomes (e.g., DLQI, WC, lipid profiles, inflammatory markers) will be presented as mean ± standard deviation for continuous variables and as frequencies (n) and percentages (%) for categorical variables. Within-group comparisons (e.g., baseline vs. Week 8) will be analyzed using paired t-tests for normally distributed data or Wilcoxon signed-rank tests for non-normally distributed data. Between-group comparisons will be performed using independent samples t-tests or Mann–Whitney U tests. Categorical outcomes will be compared using Chi-square tests (or Fisher’s exact tests). A two-sided *p*-value < 0.05 will be considered statistically significant. All analyses will follow the intention-to-treat principle. For exploratory outcomes assessed at extended time points (Weeks 12, 16, 24, and 32), the analysis will be primarily descriptive. Data are presented as mean ± standard deviation (or median with interquartile range for non-normally distributed data). No formal between-group hypothesis testing will be performed for these time points, as the data will be intended to illustrate long-term trends rather than confirm treatment efficacy. All statistical tests will be two-sided with a significance level of *α* = 0.05.

Pre-specified subgroup analyses will be performed to explore the heterogeneity of treatment effects on the primary outcomes. Interactions between treatment group and the following baseline covariates will be tested using the linear mixed model by including an interaction term: sex (male, female), age (< 45 years, ≥ 45 years), baseline BMI (< 28 kg/m^2^, ≥ 28 kg/m^2^), baseline disease duration (< 5 years, ≥ 5 years)

Analysis of AEs will be performed on the safety population, summarizing the incidence of adverse events and changes in laboratory parameters by treatment group using descriptive statistics. Formula: AEs rate (%) = (number of participants with a treatment-related adverse reaction / total number of participants receiving the treatment) × 100%. The results of subgroup analyses will be interpreted as exploratory.

No adjustment for multiple comparisons will be made for these analyses.

The analysis will handle missing data using a complete-case approach without imputation.

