### Withdrawal criteria

2.8

Participation will be discontinued if any of the following criteria are met:

(1) Failure to attend scheduled outpatient follow-ups on time.(2) Occurrence of serious adverse reactions.(3) Changes in the participant’s medical condition that render continued participation inappropriate.(4) The participant or their legal guardian requests to stop.

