#### Data handling for terminated cases

2.8.1

For participants who are withdrawn, all collected data will be retained in the case report forms. The last available observation will be used as the final outcome for both efficacy and safety analyses.

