### Sample size calculations

2.11

Based on our pilot data, the verum ACE achieved an improvement rate of 60%. Since no sham-controlled acupuncture trials for psoriasis are available, we derived the sham group response rate from the placebo effect observed in psoriasis pharmacological trials, which was approximately 25% as reported in the literature (40). Sample size estimation was performed using the standard formula for comparing two independent proportions (two-sided test, *α* = 0.05, power = 80%):

$$n1=n2=\frac{{\left(Z_{1-\alpha /2}+Z_{1-\beta }\right)}^{2}\times [p_{1}(1-p_{1})+p_{2}(1-p_{2})]}{{\left(p_{1}-p_{2}\right)}^{2}}$$

Where p_1_ = 0.60, p_2_ = 0.25, Z_1 − α/2_ = 1.96, and Z_1 − β_ = 0.84. The calculated sample size was 28 participants per group. After adjusting for a 20% dropout rate, the final sample size was determined to be 35 participants per group (total 70 participants).

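### A per-protocol analysis is named as the sensitivity check on missing-data handling, but it does not vary the missing-data assumption, so its agreement with the primary result is not evidence of robustness

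*Protocol article*

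**What the plan says.** The missing-data strategy is set in one sentence of the protocol article, section 2.21 (Statistical methods). For missing data, "preference will be given to filling in missing values using existing data through multiple imputation or mixed-effects models". The same sentence then adds a second analysis ("while also conducting per-protocol set analyses") and gives it the role of a check: "while also conducting per-protocol set analyses (including only participants with ≥ 80% compliance) as sensitivity verification". The next paragraph fixes the model for the two week-8 co-primaries, PASI and BMI: "The primary analysis will use a linear mixed-effects model for repeated measures".

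Two other rules sit beside this one. Section 2.8.1 (Data handling for terminated cases) says of withdrawn participants: "The last available observation will be used as the final outcome for both efficacy and safety analyses". Section 2.21 closes with: "The analysis will handle missing data using a complete-case approach without imputation". That last sentence follows the text on adverse events and exploratory subgroups and may be meant only for those, but the article does not limit it.

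On the amount and causes of missing data, section 2.11 (Sample size calculations) reaches its total "After adjusting for a 20% dropout rate". Section 2.8 (Withdrawal criteria) lists, among other reasons for discontinuation, "Occurrence of serious adverse reactions".

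**The concern.** A sensitivity analysis for missing data should keep the question fixed and change what is assumed about the unobserved values. Multiple imputation and mixed models, as normally applied, assume data are missing at random, although the article does not say so. The per-protocol analysis does the reverse: it changes who is analysed, using a criterion met or failed after randomization, and assumes nothing different about unseen week-8 outcomes. It is also built largely on the same observed data as the primary analysis, so the two tend to agree whether or not the missing-data assumption is sound.

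At stake is the robustness statement in the trial report. If participants who do badly leave one arm more than the other, the primary estimate can be biased, and the planned check can shift the same way and be reported as support.

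**Working it through.** **1. The plan's own figures.** Section 2.11 gives p1 = 0.60, p2 = 0.25, z = 1.96 and 0.84.

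n = (1.96 + 0.84)² × (0.60×0.40 + 0.25×0.75) / (0.60 − 0.25)² = 7.84 × 0.4275 / 0.1225 = 27.36, so 28 per arm.

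28 / 0.80 = 35 per arm. Both figures reproduce. Expected dropout is 0.20 × 35 = 7 per arm.

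**2. What the per-protocol set removes.** Section 2.13 plans four sessions. The article does not define compliance. If it means attendance, 3 of 4 is 75%, so at least 80% requires 4 of 4. At assumed miss rates per session of 2%, 5% and 10%, 35 × (1 − 0.98⁴) = 2.7, 35 × (1 − 0.95⁴) = 6.5 and 35 × (1 − 0.90⁴) = 12.0 participants per arm would be excluded. The set is then close to a completers' set, though not identical to one: someone lost after session 4 could be in it without a week-8 value, and someone who missed one session but attended week 8 would be out.

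**3. Size of the bias, by hand.** Assumptions, none given in the documents: no true effect; outcome in SD units; 20% missing at week 8 in each arm; sham dropout at random; verum dropout tilted to poor week-8 response with correlation r of 0.5 to 1.0; correlation ρ between week-4 and week-8 change of 0.5 to 0.7.

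If the lowest 20% on the dropout tendency leave, the mean of those remaining rises by r × φ(0.8416) / 0.80 = r × 0.280 / 0.80 = 0.35r.

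- Completers or per-protocol: 0.35 × 0.5 = 0.175 to 0.35 × 1.0 = 0.35 SD.
- A mixed model recovers part of this through week 4, leaving about 0.35r(1 − ρ²): from 0.175 × (1 − 0.49) = 0.09 to 0.35 × (1 − 0.25) = 0.26 SD. The true figure is slightly larger, because selection weakens the fitted week-4 slope.

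**4. Size of the bias, by simulation.** Under those settings (6,000 trials each, 35 per arm) the mixed-model bias was 0.10 to 0.28 SD (0.09 to 0.28 in a rerun) and the per-protocol bias 0.17 to 0.34 SD, in line with step 3.

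**5. When it does and does not arise.** A second simulation used 35 per arm, ρ = 0.7, no true effect and 20% dropout unless stated. Per-protocol is taken as compliant completers. The false-positive columns count only results favouring verum (nominal 2.5%).

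| Dropout | Bias, mixed model | Bias, per-protocol | False positive, mixed model | False positive, per-protocol | Per-protocol agrees with a false positive |
|---|---|---|---|---|---|
| Completely at random | 0.00 | 0.00 | 2.4% | 2.4% | 69% |
| Depends on week 8, same in both arms | 0.00 | 0.00 | 2.1% | 2.5% | 74% |
| Depends on week 4, verum only | +0.005 | +0.22 | 2.7% | 14.0% | 100% |
| Depends on week 8, verum only | +0.18 | +0.31 | 11.0% | 24.0% | 98% |
| Depends on week 8, 30% verum, 10% sham | +0.16 | +0.27 | 11.0% | 22.0% | 97% |
| Depends on week 8, verum only; good verum responders also non-compliant (4,000 runs) | +0.18 | +0.07 | not tabulated | not tabulated | not tabulated |

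Per-protocol can therefore endorse a biased primary result (rows 4 and 5) or depart from a sound one (row 3). Neither agreement nor disagreement shows whether the missing-data assumption holds.

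**6. Baseline for agreement.** In the settings of step 3, per-protocol agreed with 84 to 98% of false positives. With data missing completely at random the corresponding figure was already about 75 to 84% (69% in the table, where only verum-favouring results count). Most of the agreement reflects shared data.

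**7. A grid that covers the range.** With 7 of 35 verum values imputed, worsening each by δ SD moves the verum mean by (7/35)δ = 0.2δ. A grid of 0 to 1.5 SD spans 0 to 0.30 SD, which covers the mixed-model bias of up to 0.28 SD.

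**The case against.** Several points on the other side are sound.

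- **Scope.** The article refers to a separate statistical analysis plan that is not shown, and tipping-point or reference-based analyses commonly sit there. A reader might infer that the trial has no other sensitivity analysis; the documents do not support that. What stands is narrower: the role given to per-protocol is stated here, in the missing-data sentence itself.
- **Convention.** Pairing an intention-to-treat with a per-protocol analysis is usual, and the article never says that per-protocol tests missing at random. Running it is unobjectionable; using it to verify the missing-data handling is the problem.
- **Mechanism.** Participants are blinded and the sham differs only in the absent suture. With no effect and blinding intact, leaving for poor response should be similar in both arms, and then neither analysis is biased. A reader might point to suture expulsion or induration as verum-only reasons to leave. Section 2.22 (Harms) gives management for these and stops only for allergic reaction or shock, section 2.8 names only serious reactions among adverse events, and nothing links such events to poor response. Arm-differential, outcome-related dropout is possible but assumed.
- **Which primary.** Under last observation carried forward, per-protocol does change the handling of missing values, but together with the population, so a difference could not be attributed to either. Under complete case, per-protocol is a near-subset of the primary and still less independent of it.
- **Overlap.** Section 2.18 (Retention strategies) plans an early termination visit to collect efficacy outcomes, so dropouts may have late data. Per-protocol would discard those data for anyone below the compliance threshold.

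**Conclusion.** The point holds in a limited form: the named check cannot do the job assigned to it. This follows from what a per-protocol set is and does not depend on any simulation.

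The possible harm is conditional. With 20% dropout that is response-related in the verum arm only, and no true effect, bias towards ACE is about 0.1 to 0.3 SD for the mixed model and 0.17 to 0.34 SD for per-protocol. The SD scale, the correlations and the dropout mechanism are assumptions.

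Two stronger readings are tempting and are not supported. The first is that per-protocol is more biased than the primary analysis: the two are equally unbiased when the arms share mechanism and rate, and per-protocol is less biased when non-compliance selects the other way (+0.07 against +0.18 SD). The second is that it will confirm a false result: it may, and agreement of 84 to 98% must be read against about 75 to 84% when nothing is wrong.

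This is an inexpensive improvement that should be made. It does not invalidate the design.

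**What to change.** 1. Reconcile section 2.8.1 (last observation) and the two statements in section 2.21 (multiple imputation or mixed model; complete case) into one primary rule for PASI and BMI at week 8. If complete case is meant only for exploratory or safety analyses, say so. No sensitivity analysis can be specified until this is settled.
2. Replace the label given to the per-protocol analysis in section 2.21 with an analysis that varies the missing-data assumption for both co-primaries. Suitable choices are delta-adjusted multiple imputation that worsens imputed verum values in steps from 0 to 1.5 SD, with the tipping point reported, or reference-based imputation in which verum dropouts follow the sham distribution, or both.
3. Keep the per-protocol analysis as supplementary and define compliance, including whether the threshold means all four sessions.

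The cost is wording in the protocol and analysis plan plus some programming, with no extra data. The downside is that the robustness statement may turn out less favourable.
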